### Randomization and blinding

Patients will be randomly assigned (on a 1:1 ratio) to the more frequent acupuncture treatment group (group M) or the less frequent acupuncture treatment group (group L). The randomization sequence will be computer generated by independent research staff with SAS 9.3 software, using block randomization with a block size of six via a central randomization system. The randomization sequence will be embedded into the software (Beijing Guide Technology Co, Ltd). The CRC will input the patient information on a tablet computer and will be given a random number. The randomization protocol will be designed by a statistician ([name]) of Fuwai Hospital, China Academy of Medical Science who is not involved in the later statistical work of the study.

The outcome assessor and data analyst will be blinded to group assignments. The acupuncturist and patients will not be blinded because of the nature of the intervention. Patients’ allocated interventions will not be revealed until the statistical analysis is completed.

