#### Secondary outcome measurements

Knee pain will be assessed by the NRS and the WOMAC pain subscale (five items, scored from 0 to 20, higher scores indicating worse pain) at weeks 4, 8 and 16. The WOMAC function subscale will be used to measure physical function at weeks 4, 8 and 16. The WOMAC stiffness subscale will be used to measure the degree of stiffness experienced in the knee at weeks 4, 8 and 16. The Overall Treatment Effect will be used to measure the overall acupuncture treatment effect at weeks 4 and 8. The 12-item Short Form Health Survey [32] (SF-12; scored from 0 to 100, higher scores representing better quality of life) will be used to measure the quality of life at weeks 4, 8 and 16. The Expectation and Credibility of treatment rating scale [33] will be used to measure the patients’ attitudes to acupuncture after the first treatment. The number of adverse events and severe adverse events and the usage of Tylenol will be recorded from baseline to week 16.

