### Sample size

The current study is designed as a pilot study to explore symptomatic improvement in patients with knee osteoarthritis receiving 3 sessions per week of acupuncture compared to 1 session per week. Acupuncture as a complex intervention is different from drugs. If the acupoints in the study were changed, then the effectiveness of the acupuncture would be altered. Consequently, we do not use data from the literature to calculate the sample size. We based our sample size on the response rate. Based on our previous study (unpublished) and clinical experience, the sample size is calculated to provide 80% power if 70% of group M achieved a decrease ≥ 2 points on the NRS and a decrease ≥ 6 points in WOMAC function score at 8 weeks, compared with 30% of group L, at a two-tailed α level of 0.05. This requires a total of 60 participants, allowing for 20% dropout.

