### Statistical analysis

Analyses will be intention-to-treat (ITT), with all patients included in their assigned treatment group and receiving at least one session treatment. The level of significance will be set at 0.05 (two-sided). Patients’ baseline characteristics will be summarized by treatment arm. For continuous outcomes, the data will be presented as mean (standard deviation) or the median (interquartile range) according to the normality of the distribution. Enumeration data will be presented as a percentage. For the primary outcome, we will calculate the response rates at 8 weeks and compare group M and group L using the χ^2^ test. For secondary outcomes, continuous variables including WOMAC pain, function and stiffness scores, NRS, SF-12, the Expectation and Credibility of acupuncture treatment and Overall Treatment Effect will be compared between the two groups at all follow-up time points using an unpaired Student’s *t* test or Wilcoxon rank-sum test as appropriate. For the dropout analysis, we will use the last observation carried forward method. SPSS version 21.0 (IBM SPSS Statistics, New York, USA) will be used for statistical analysis.

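### Last observation carried forward is a weak rule for the week-8 responder endpoint and can bias the M–L difference in either direction if dropout differs by arm

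*Protocol article*

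**What the plan says.** The Statistical analysis section of the protocol article keeps every patient who had at least one session in the assigned arm. For the primary outcome it states: "we will calculate the response rates at 8 weeks and compare group M and group L using the" chi-square test. On missing data it says only: "For the dropout analysis, we will use the last observation carried forward method". It names no other method and no sensitivity analysis.

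A primary responder must improve by at least 2 units on the pain NRS and by at least 6 units on WOMAC function, from baseline to week 8. Under Secondary outcome measurements, function is scheduled thus: "The WOMAC function subscale will be used to measure physical function at weeks 4, 8 and 16". The NRS follows the same schedule. Week 4 is therefore the only assessment between baseline and the primary endpoint.

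The Sample size section expects losses: "This requires a total of 60 participants, allowing for 20% dropout". It gives no dropout rate by arm. Under Interventions, group M has three sessions a week for 8 weeks (24) and group L has one (8). The Randomization and blinding section says that patients are not blinded.

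**The concern.** Carrying an observation forward replaces an unknown week-8 response with something else. A patient who leaves before week 4 carries baseline, shows zero change and is counted as a non-responder. A patient who leaves between weeks 4 and 8 is scored halfway through treatment. Neither value estimates week-8 response, and both enter the chi-square test as if they had been observed.

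If the same share of patients is lost in each arm and the carried values respond equally, a comparison with no true effect is not shifted. If either differs by arm, it is shifted. A threefold difference in visits among patients who know their arm makes unequal dropout plausible. At stake is the M–L response difference, which the Discussion says will inform whether a full-scale trial is run.

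**Working it through.** **Inputs from the protocol article.** Response 70% in M and 30% in L, 80% power, two-sided alpha 0.05, 20% dropout, total 60, 1:1 allocation (Sample size; Randomization and blinding). Primary test: chi-square on week-8 response (Statistical analysis).

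**Inputs assumed, because the protocol does not give them.** Dropout by arm, and the response rate among carried-forward values.

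**1. The plan's own figure.** Two-proportion formula with pooled variance under the null and no continuity correction:

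n = [1.960·√(2·0.5·0.5) + 0.842·√(0.7·0.3 + 0.3·0.7)]² / 0.4² = 23.3, so 24 per arm.

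24 / 0.8 = 30 per arm, 60 in total. The stated sample size reproduces.

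**2. Analysed response rate under carry-forward.** Let p be an arm's true week-8 rate, d its dropout, and q the response rate among its carried values. Dropouts are assumed to have the same true week-8 rate p as completers.

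Analysed rate = (1 − d)·p + d·q

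If every dropout carries baseline, q = 0. Rejection rates and power below come from exact enumeration of the uncorrected chi-square test with 30 per arm.

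**3. No true effect, p = 0.50 in both arms, q = 0.**

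| Dropout M / L | Analysed M | Analysed L | Difference | Rejection |
|---|---|---|---|---|
| 20% / 20% | 0.8·0.5 = 40% | 0.8·0.5 = 40% | 0 | about 5% |
| 30% / 10% | 0.7·0.5 = 35% | 0.9·0.5 = 45% | −10 points | 12.2% |
| 10% / 30% | 0.9·0.5 = 45% | 0.7·0.5 = 35% | +10 points | 12.2% |

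Without dropout (50% versus 50%) the test rejects 5.2% of the time. A milder 25% / 15% split gives 37.5% versus 42.5%, a difference of −5 points.

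If half the dropouts leave after week 4 and 35% of those are responders at week 4, q = 0.5·0.35 = 0.175. The 30% / 10% split then gives 0.35 + 0.3·0.175 = 40.25% versus 0.45 + 0.1·0.175 = 46.75%. That is −6.5 points, with 8.0% rejection.

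**4. Planned effect, p = 0.70 and 0.30, equal 20% dropout.**

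| Carried values | Analysed M | Analysed L | Difference | Power |
|---|---|---|---|---|
| Respond at the arm's week-8 rate | 70% | 30% | 40 points | 89.6% |
| Respond at half that rate | 0.56 + 0.2·0.35 = 63% | 0.24 + 0.2·0.15 = 27% | 36 points | 82.2% |
| All baseline (q = 0) | 0.8·0.7 = 56% | 0.8·0.3 = 24% | 32 points | 72.9% |

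With a true effect, the difference shrinks even under balanced dropout unless carried values respond at the week-8 rate.

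**5. Planned effect, unequal dropout, q = 0.** A 30% / 10% split gives 49% versus 27%, 22 points, power 41.6%. The reverse split gives 63% versus 21%, 42 points. Carry-forward is therefore not reliably conservative.

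**The case against.** The strongest reply is that the bias is conditional. The protocol states 20% dropout overall and says nothing about arms. With equal dropout and equal carried-forward response the null comparison is untouched. This stands. The split of 30% and 10% is an illustration, and if M loses more patients the bias works against the trial's own hypothesis.

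The false differences also assume that dropouts would have responded like completers. If patients leave because treatment is failing, scoring them as non-responders may be close to the truth. Visit burden bears first on stopping sessions, and a patient who stops may still complete the week-8 questionnaires. Free treatment is a stated retention measure. All of this limits how firmly the size can be stated. It does not make a week-4 or baseline value a sound estimate of week-8 response.

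The phrase dropout analysis does not name the primary outcome. It is the only rule given, however, and nothing exempts the primary outcome, so reading it as covering that outcome is reasonable but not certain.

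A reader might infer that the sample size contradicts the analysis, because 24 per arm is inflated to 30 and all 30 are then analysed. It does not. Enrolling extra patients against losses and then analysing everyone as assigned is ordinary planning, and the power range in step 4 (72.9% to 89.6%) brackets the stated 80%.

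A reader might also infer that carrying week-8 values to week 16 exaggerates durability. It does assume no change over 8 weeks without treatment. The Background, however, says that acupuncture effects are maintained over time, and the comparison of arms is biased only if fading or missingness differs between them. The documents give no figure for this.

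**Conclusion.** The point holds in conditional form. The protocol fixes a single-imputation rule that suits a week-8 responder endpoint poorly, and that rule can bias the M–L difference in either direction if dropout or carried-forward response differs by arm. On the assumptions shown, a 20-point imbalance in dropout with all dropouts carrying baseline moves a null comparison by 10 points and raises rejection from about 5% to 12.2%. With the planned effect and balanced 20% dropout, the expected difference falls to between 32 and 36 points when carried values respond at between none and half of the week-8 rate.

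It would go too far to say that the primary comparison will be biased, or that the bias favours one arm, because the protocol supports neither. Since the trial is an exploratory pilot and the size rests on assumed dropout patterns, this is a change that should be made rather than one that must be, with moderate confidence.

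**What to change.** State which outcomes the missing-data rule covers, and replace carry-forward before outcomes are analysed by arm:

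- **Primary outcome.** Multiply impute week-8 NRS and WOMAC function from arm, baseline and week-4 scores, derive response in each completed data set, and pool.
- **Sensitivity analysis.** Report the primary comparison with missing week-8 patients counted as non-responders. This is a bounding analysis: under unequal dropout it has the same −10 or +10 point shift as the worst case above, so it should not become the primary method.
- **Continuous outcomes measured at weeks 4, 8 and 16.** Use a repeated-measures mixed model without single imputation.
- **Reporting.** Give the number missing at week 8, with timing and reasons, by arm.

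The cost is a change of analysis wording and a little programming. No added patients, visits or measurements are needed. The downside is that the non-responder sensitivity analysis has about 73% power at 20% dropout (56% versus 24%), below the stated 80%. With about 24 completers per arm, the gain in precision from multiple imputation may be small. The case for it is that its assumption is explicit and it does not treat week-4 or baseline values as week-8 results.

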### Ethics and dissemination

Ethics approval was obtained from the Research Ethical Committee of Beijing Hospital of Traditional Chinese Medicine Affiliated to Capital Medical University (No. 2017BL-076-01). This trial has also been registered on ClinicalTrials.gov (No. NCT03359603) and will be reported in compliance with the CONSORT statement as well as Standards for Reporting Interventions in Clinical Trials of Acupuncture (STRICTA) [34]. Patients are included after receiving information about the study and signing the informed consent. The results of the pilot study will be disseminated in a peer-reviewed journal.

## Discussion

This study is designed to explore an effective acupuncture method for knee osteoarthritis.

We chose a frequency of 3 sessions per week as one kind of electro-acupuncture intervention, because 3 sessions per week is most commonly used in clinical practice in China to treat chronic pain. We chose a frequency of once per week as another intervention, because electro-acupuncture treatment once per week was usually used in previous studies. The study is a single-site randomized clinical trial. A single-site trial might be helpful in the aspect that the quality of the study procedure will be better controlled in a single site than in multiple sites. One potential limitation of this study is that the unblinded treatment might theoretically influence reporting or measurement of the outcomes, thus introducing bias. Therefore, we will use an Expectation and Credibility of treatment rating scale to measure the patients’ attitudes to acupuncture.

The information obtained from the exploratory study will inform the decision to conduct a full-scale randomized controlled trial to test the frequency dependence of acupuncture, which will add to the current small body of high-quality evidence that is available on the optimal number of sessions of acupuncture for the management of knee osteoarthritis.

## Trial status

This trial is currently recruiting patients.

## Data Availability

The full protocol for the study will be available from the corresponding author. Datasets generated or analyzed during the current study will not be publicly available due to data privacy. Results from the trial will be published in peer-reviewed international journals and positive, negative and inconclusive results will be published.

## Abbreviations

ACR: American College of Rheumatology
CONSORT: Consolidated Standards of Reporting Trials
CRC: Clinical research coordinator
CRF: Case Report Form
ITT: Intention to treat
NRS: Numerical rating scale
STRICTA: Standards for Reporting Interventions in Clinical Trials of Acupuncture
WOMAC: Western Ontario and McMaster Universities Osteoarthritis Index
